## Abstract

**Background:**

The exact pathophysiology of atrial fibrillation (AF) remains incompletely understood and treatment of AF is associated with high recurrence rates. Persistence of AF is rooted in the presence of electropathology, defined as complex electrical conduction disorders caused by structural damage of atrial tissue. The atrial fibrillation fingerprinting (AFFIP) study aims to characterize electropathology, enabling development of a novel diagnostic instrument to predict AF onset and early progression.

**Hypotheses:**

History of AF, development of post‐operative AF, age, gender, underlying heart disease, and other clinical characteristics impact the degree of electropathology.

**Methods:**

This study is a prospective observational study with a planned duration of 48 months. Three study groups are defined: (1) patients with (longstanding) persistent AF, (2) patients with paroxysmal AF, and (3) patients without a history of AF, all undergoing open‐chest cardiac surgery. Intra‐operative high‐resolution epicardial mapping is performed to identify the patient‐specific electrical profile, whereas the patient‐specific biological profile is assessed by evaluating proteostasis markers in blood samples and atrial appendage tissue samples. Post‐operative continuous rhythm monitoring is performed for detection of early post‐operative AF. Late post‐operative AF (during 5‐year follow‐up) is documented by either electrocardiogram or 24‐hour Holter registration.

**Results:**

The required sample size for this study is estimated at 447 patients. Up till now, 105 patients were included, of whom 36 have a history of AF.

**Conclusion:**

The AFFIP study will elucidate whether electrophysiological and structural characteristics represent a novel diagnostic tool, the AF fingerprint, to predict onset and early progression of AF in cardiac surgery patients.

## INTRODUCTION

1

Atrial fibrillation (AF) is the most common cardiac arrhythmia worldwide, and its incidence^1^ and associated medical health care costs^2^ continuously increase. Even though numerous predisposing factors for progression of AF have been identified, the exact pathophysiology remains incompletely understood and treatment of AF is associated with high recurrence rates. As disease progression from recurrent intermittent episodes to finally permanent AF is accompanied by a gradual increase in therapy failure, early recognition of AF is of prime importance. Persistence of AF is rooted in the presence of electropathology, which is defined as complex electrical conduction disorders caused by structural damage of atrial tissue. Therefore, early recognition of AF susceptibility in patients is necessary to halt electropathology and hence disease onset and progression. Although promising artificial intelligence applications are emerging,^3^ up till this day in clinical practice, AF is diagnosed with a surface electrocardiogram when a patient already suffers from AF. This rhythm registration cannot assess the degree of electropathology and thus the stage of AF which is essential for selection of the appropriate therapy. Hence, early recognition of AF and the start of effective treatment is seriously hampered. By characterizing electropathology, we aim to develop a novel diagnostic instrument to predict AF onset and early progression. We hypothesize that every patient has a unique biological and electrical signal profile that is influenced by age, gender and underlying heart disease. This bio‐electrical profile is deduced from the ratio abnormal/normal electrical signals in the atria by utilizing a unique high‐density atrial mapping approach and determination of proteostasis markers in tissue or blood samples related to structural damage. These outcomes are summarized in an AF Fingerprint.

Multi‐site high density epicardial mapping has been used in multiple research protocols in Rotterdam (QUASAR study MEC 2010‐054, HALT&REVERSE study MEC 2015‐393), Leiden and Maastricht.^4^, ^5^, ^6^, ^7^ Since 2010, the mapping procedure is daily practice in the Erasmus Medical Center. Atrial conduction during both sinus rhythm (SR) and (induced) AF can be visualized to identify the patient‐specific electrical profile. This alone however does not clarify electropathological changes on structural level that contribute to substrate for AF. Previous studies revealed that structural damage is caused by derailment of protein homeostasis due to loss of key modulators within the protein quality system.^8^ Failure of protein quality control in AF involves impairment of heat shock proteins (HSPs),^9^ autophagy,^10^ loss of sarcomeric and microtubule proteins,^11^, ^12^ and activation of DNA damage/PARP1/NAD axis,^13^ favoring progression of AF.

The AFFIP study combines electrophysiological and structural alterations into one AF fingerprint (Figure 1). Electrophysiological data obtained from epicardial mapping during surgery are combined with proteostasis markers on one hand and atrial tissue characteristics on the other hand. By comparing the bio‐electrical AF fingerprint of patients from different age groups, gender, history of AF, development of post‐operative AF, underlying heart disease and other clinical characteristics, we hope to gain more insight in the mechanism underlying AF and the development of a substrate for AF. The findings will elucidate whether structural and electrophysiological characteristics represent a novel diagnostic tool, the AF fingerprint, to predict onset and early progression of AF in cardiac surgery patients.

**FIGURE 1 clc23370-fig-0001:**
[figure not shown]
Concept of the atrial fibrillation fingerprinting (AFFIP) study. The AFFIP study hypothesizes that every patient has a unique biological and electrical signal profile that is influenced by age, gender and heart disease. Intra‐operative high‐resolution epicardial mapping is performed to identify the patient‐specific electrical profile, whereas the biological profile is assessed by evaluating proteostasis levels in blood samples and atrial appendage tissue samples. Derailment of protein homeostasis can lead to structural remodeling, favoring inhomogeneous conduction and progression of atrial fibrillation (AF). We aim to develop a novel diagnostic tool, the bio‐electrical AF Fingerprint, to predict onset and early progression of AF

## METHODS

2

AFFIP is a prospective observational study, with a planned duration of 48 months. This study is carried out according to the principals of the Declaration of Helsinki and in accordance with the Medical Research involving Human Subjects Acts. The study is part of the HALT&REVERSE protocol which is approved by the Rotterdam local medical ethical committee (MEC‐2014‐393).

### Study objectives

2.1

The primary study objectives are to test the correlation between the AF fingerprint, revealing the degree of electropathology including for example, patterns of activation and signal morphology, proteostasis levels and atrial tissue characteristics, clinical characteristics and onset and progression of AF in patients undergoing open‐chest cardiac surgery.

### Study population

2.2

Patients with structural heart disease scheduled for elective cardiac surgery are included. The study population consists of three study groups: patients with (longstanding) persistent AF (group 1), patients with paroxysmal AF (group 2) and patients without a history of AF (group 3) undergoing open‐chest cardiac surgery. In line with ESC guidelines, patients with documentation (ECG or ECG description) of self‐terminating AF episodes up to 7 days, or with AF episodes cardioverted within 7 days are classified as paroxysmal AF. Patients with documentation of AF episodes longer than 7 days or longer than a year are classified as persistent and longstanding persistent AF, respectively. Patients are recruited at the Department of Cardiothoracic Surgery at the Erasmus Medical Center, Rotterdam, The Netherlands. Prior to enrolling in the study, each patient is provided an oral and a written explanation of the study procedure. Written informed consent is obtained from all patients.

Prior to cardiac surgery, blood samples are taken from all patients for determination of proteostasis levels (Figure 2). Patient characteristics (eg, age, medical history, and cardiovascular risk factors) are obtained from the patient's file.

**FIGURE 2 clc23370-fig-0002:**
[figure not shown]
Time course of the atrial fibrillation fingerprinting (AFFIP) study. A baseline blood sample (red bar) is obtained from all patients 1 day prior to surgery. During surgery, the study procedure (blue bar, epicardial mapping) is performed, followed by post‐operative continuous rhythm monitoring (orange bar). Patients are consulted by phone at 6 months, 12 months, and yearly up to 5 years after surgery for detection of late post‐operative atrial fibrillation (AF) (green bars)

### Inclusion criteria

2.3

In order to be eligible to participate in this study, a subject must meet all of the following criteria:at least 18 years of age;structural heart disease (with or without history of AF); andscheduled for elective cardiac surgery.

### Exclusion criteria

2.4

A potential subject who meets any of the following criteria is excluded from participation in this study:hemodynamic instability;emergency cardiac surgery; andredo‐cardiac surgery.

Additional details of entry criteria are listed in the Appendix S1.

### Intra‐operative mapping procedure

2.5

Epicardial mapping is performed during surgery. Patients are under full anesthesia and vital signs are monitored continuously throughout the procedure. Epicardial unipolar electrograms are recorded using a custom‐made multi‐site electrode array. Recordings are made at nine consecutive sites (right atrium 1‐4, Bachmann's bundle, right and left pulmonary vein, and left atrium 1‐2), following a predefined mapping scheme (Figure 3) during SR (nine sites, 5 seconds/site), during pacing maneuvers for inducing AF (one site, Bachmann's bundle), and in AF (nine sites, 10 seconds/site). Pacing is performed with atrial fixed rate pacing directly from the electrode or with a standard temporary pacemaker wire. If AF sustains at the end of the mapping procedure, SR is restored with 5‐10 J electrical cardioversion.

**FIGURE 3 clc23370-fig-0003:**
[figure not shown]
Epicardial mapping to retrieve unipolar atrial electrograms. With the use of a 192 electrode arrays, the left atrium (LA), right atrium (RA), pulmonary vein (PV) area, and Bachmann's bundle (BB) are mapped following this predefined mapping scheme. Unipolar atrial electrograms are collected during sinus rhythm (SR), pacing maneuvers (P), and (electrically induced) atrial fibrillation (AF). Morphology of atrial potentials are subdivided into four categories: single potentials (one deflection), short double potentials (two deflections less than 15 ms apart), long double potentials (two deflections 15 ms or more apart), and complex fractionated potentials (three or more deflections). ICV, inferior caval vein; LAA, left atrial appendage; PVL, left pulmonary vein area; PVR, right pulmonary vein area; RAA, right atrial appendage; SCV, superior caval vein

After introduction of the extra corporal circulation into the right atrium via the right atrial appendage (RAA) a tissue sample (approximately 10 × 10mm) is obtained from the incision site in all patients. In patients undergoing mitral valve surgery, the left atrial appendage (LAA) is also incised and a small tissue sample is excised. In patients undergoing surgical pulmonary vein isolation, a left sided procedure in patients with AF which includes amputation of the LAA, the LAA tissue is also studied.

### Follow‐up

2.6

After procedure, the heart rhythm is continuously monitored until hospital discharge in order to detect early post‐operative AF. Patients are also consulted by phone at 6 months, 12 months, and yearly up to 5 years after surgery in order to detect late post‐operative AF (Figure 2). If post‐operative AF is suspected, documentation of electrocardiography, 24‐hour Holter registration or a clinical discharge letter from peripheral hospitals are retrieved.

### Tissue analysis

2.7

All obtained blood samples and atrial tissue samples are stored at ‐80°C until transport to the Amsterdam UMC, location VU Medical Center. Proteostasis markers include HSP27, HSP70, HSPA1A, HSPA5, HSPB1, HSPB5, HSPB6, HSPB7, HSPB8, HSPD1, α‐SMA, LC3B‐II, TIMP1, LOX3, MMP9, Galectin‐3, NCAM, MT‐ND1, and COX3, and are determined by commercially available ELISAs and Western blot analysis at the Department of Physiology of the Amsterdam UMC.

### Main study parameters and endpoints

2.8

Primary endpoint of the study is development or recurrence of AF. Secondary endpoints include implantation of an atrial pacemaker or implantable cardioverter defibrillator. Additional secondary endpoints are described in the Appendix S1. At present, no substudies are planned.

Deflections of the recorded atrial electrograms are detected semi‐automatically in custom‐made Python 3.6 software. In case of fractionated electrograms, the component with the steepest negative slope is taken as the local activation time (Figure 3). Electrograms with injury potentials and artifacts are excluded from analysis by consensus of two investigators. Signals are used to construct color‐coded activation, conduction block, break‐through wave, fractionation, and voltage maps (Figure 4). Furthermore, the relation between patterns of activation, incidence of breakthrough waves, fractionation, fibrillation intervals, conduction abnormalities, and voltage is studied and compared between the different atrial sites and atrial rhythms. Electrical changes as defined with the above‐mentioned electrical parameters will be correlated with the pre‐operative proteostasis levels, development of post‐operative AF, age, gender, and other clinical characteristics.

**FIGURE 4 clc23370-fig-0004:**
[figure not shown]
Construction of the atrial fibrillation fingerprint (AFFIP). The left panel shows an example of an activation map during electrically induced atrial fibrillation (AF) of the left pulmonary vein area in a patient undergoing coronary artery bypass grafting without a history of AF. Isochrones are drawn at 5 ms, areas of conduction block (Δ local activation time [LAT] ≥ 12 ms) are indicated by black bars and the origin of peripheral waves by gray dots. The arrows indicate main activation direction. The corresponding fractionation map is displayed in the right panel and shows the different types of atrial potential morphologies: single potentials (SP, one deflection), short double potentials (sDP, two deflections less than 15 ms apart), long double potentials (lDP, two deflections 15 ms or more apart) and complex fractionated potentials (CFP, three or more deflections). The maps are used to determine the incidence of for example, fractionation and conduction block

The primary hypothesis is that the degree of electropathology will be increased in patients with a history of AF and patients whom develop post‐operative AF. Secondarily, we hypothesize that age, gender, underlying heart disease and other clinical characteristics impact the degree of electropathology.

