### Statistical analysis

2.10

Associations between proteostasis markers, electrical signals and clinical patient outcomes are calculated using multivariate logistic regression and cox regression models. Log rank tests compare patient groups with different stages of AF. Continuous and categorical electrophysiological parameters are compared with respectively ANOVA and chi‐square tests. For repeated biomarker measurements, joint modeling and mixed modeling analysis is used. ANOVA with Bonferroni adjustments corrects for analysis of multiple biomarkers.

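### No method named in the plan adjusts the comparison of electropathology by AF history, although the protocol itself expects age, gender and heart disease to affect electropathology

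*Protocol article*

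**What the plan says.** Section 2.8 (Main study parameters and endpoints) sets the primary hypothesis: "The primary hypothesis is that the degree of electropathology will be increased in patients with a history of AF", and likewise in those who develop AF after surgery. The secondary hypothesis follows directly: "we hypothesize that age, gender, underlying heart disease and other clinical characteristics impact the degree of electropathology".

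Section 2.2 defines three groups by AF history: (longstanding) persistent, paroxysmal and none.

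Section 2.10 gives the methods. For electrophysiological parameters: "Continuous and categorical electrophysiological parameters are compared with respectively ANOVA and" chi-square tests, with no covariates. For outcomes: "Associations between proteostasis markers, electrical signals and clinical patient outcomes are calculated using multivariate logistic regression and cox regression models". Biomarkers get ANOVA with a Bonferroni correction, and joint and mixed models are kept for repeated biomarker measurements. Section 2.8 adds that the electrical "parameters will be correlated with the" pre-operative marker levels, post-operative AF, age, gender and other characteristics.

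Two further statements in section 2.5 matter. Mapping is planned at nine sites in sinus rhythm and at nine sites in AF. Right atrial appendage (RAA) tissue is taken from everyone, but left atrial appendage (LAA) tissue is not: "In patients undergoing mitral valve surgery, the left atrial appendage (LAA) is also incised and a small tissue sample is excised". The other LAA source is surgical pulmonary vein isolation, which is described as a procedure in patients with AF.

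**The concern.** AF history is observed, not assigned. If the AF groups are older or have a different mix of heart disease, and those factors change electropathology as the protocol expects, an ANOVA by AF group returns the sum of two things: what goes with AF history and what goes with case mix. The study could then report a case-mix difference as support for the AF-history half of its primary hypothesis. A larger sample does not help, because the bias stays the same while the standard error shrinks.

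Two design features call for the same like-for-like discipline. Parameters are recorded in more than one rhythm, and nothing says that AF-history groups are compared within one rhythm. LAA samples come from patients selected by operation or by AF itself, so an LAA marker difference between groups would mix AF history with type of surgery.

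**Working it through.** **Step 1: which named method could adjust the AF-history contrast?** The contrast needs electropathology as the dependent variable, AF group as the factor, and age, gender and heart disease as covariates.

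- ANOVA and chi-square (section 2.10): electropathology is the dependent variable, but no covariates are named, and a chi-square test takes none.
- Logistic and Cox models: covariates are possible, but the dependent variable is a clinical outcome. They do not estimate mean electropathology by AF history.
- Bonferroni-adjusted ANOVA: this corrects for the number of biomarkers, not for confounding.
- Joint and mixed models: reserved for repeated biomarker measurements.
- Correlation with age and gender (section 2.8): this describes those relations one at a time and does not adjust the group contrast.

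None fits.

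**Step 2: the plan's own numbers.** Section 2.9 gives 135 per group. With 10% added, 135 × 1.10 = 148.5, so 149 per group, and 3 × 149 = 447, as stated. The 135 itself cannot be reproduced because the pilot effect size and SD are not given. It is used below only as the group size.

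**Step 3: illustration of size.** The documents give neither the between-group covariate gap nor its correlation with electropathology. Table 1 shows a mixed cohort (median age 64, quartiles 54 and 71; 42% congenital heart disease) but is not split by AF group. So these are assumptions:

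- covariate gap D = 0.5 SD between no AF and persistent AF, with paroxysmal AF midway;
- covariate–parameter correlation b = 0.2, 0.3 or 0.4;
- parameter SD taken as 1, and no AF-history difference beyond the covariate.

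Group means are then D·b, D·b/2 and 0. The noncentrality of the three-group F test is λ = 135 × 2 × (D·b/2)². The test has 2 and 3 × 135 − 3 = 402 degrees of freedom, alpha 0.05, and a critical F of 3.018.

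| b | D·b (SD) | λ | Rejection rate |
|---|---|---|---|
| 0.2 | 0.10 | 135 × 2 × 0.05² = 0.675 | 10.4% |
| 0.3 | 0.15 | 135 × 2 × 0.075² = 1.519 | 17.9% |
| 0.4 | 0.20 | 135 × 2 × 0.10² = 2.700 | 29.1% |

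The result depends strongly on D. With D = 0.25 the range is 6.3% to 10.4%; with D = 0.75 it is 17.9% to 58.6%. A correctly specified adjusted model would stay at about 5%.

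**The case against.** **The article does not say that the primary hypothesis is tested by unadjusted ANOVA.** Section 2.10 names no grouping factor for the ANOVA, and section 2.8 also speaks of comparisons between atrial sites and rhythms. This stands: the link is not explicit. But ANOVA and chi-square are the only tests named for comparing these parameters, and no other named method supplies the adjusted contrast.

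**Covariates may be listed in the full protocol or an analysis plan.** They may, and a missing list would be no finding. The point is the test that the article does name, which does not suit the hypothesis beside it.

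**The multivariable models cover the main outcome.** This stands for post-operative AF, and for the primary endpoint of AF development or recurrence. It does not reach pre-existing AF history.

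**The hypothesis is one of association.** As worded, an age-driven difference between groups is a real difference, so the rates above are not false positives for the marginal hypothesis. This stands, and they are stated accordingly as rejections with no difference beyond the covariate. Yet the Introduction seeks insight into mechanism by comparing patients by age, gender, AF history and heart disease, which requires separating these contributions.

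**Stronger readings that the documents do not support.** From "If AF sustains at the end of the mapping procedure, SR is restored" a reader might infer that AF-history patients are mapped in spontaneous AF, the others in induced AF, and that the maps are pooled. The article does not say how patients arriving in AF are handled, plans both rhythms without distinguishing groups, and plans no pooling. Nor does it plan a between-group LAA comparison. Tissue source bears on tissue markers, not on electrogram parameters, and RAA tissue from all patients allows a like-for-like comparison. A two-group z test would give a higher rate (23% at 0.15 SD), but that is not the test the plan names.

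**Conclusion.** The point holds for the AF-history half of the primary hypothesis. The plan compares electropathology between non-randomised groups, expects other patient factors to affect it, and names no method that adjusts for them. This should be changed, because the named test lets case mix pass as an AF-history difference. The direction and size of any bias cannot be derived from the documents. The 10% to 29% illustration rests wholly on the assumed 0.5 SD gap with paroxysmal AF midway, correlations of 0.2 to 0.4, and 135 patients per group. On rhythm and tissue the supportable statement is narrower: a like-for-like rule should be stated, but the article does not show that unlike recordings or samples will be compared.

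**What to change.** In section 2.10, make the primary AF-history comparison a linear regression of each electropathology parameter on AF group, adjusted for age, sex and underlying heart disease. Use a mixed model where several sites per patient enter. Categorical parameters need the corresponding logistic form, with the parameter as the dependent variable. Keep the unadjusted ANOVA and chi-square results as descriptive. State that groups are compared within the same recording rhythm, and that the between-group tissue-marker comparison uses RAA tissue.

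Age, gender and underlying heart disease are already collected (Table 1), so for the covariates only the analysis wording changes. The cost in degrees of freedom is small at full size. Age, sex and the seven heart-disease categories of Table 1 take 1 + 1 + 6 = 8, leaving 402 − 8 = 394 at 135 per group. Numbers will be smaller within each rhythm. Of the 105 patients enrolled so far, 20 have paroxysmal AF, 14 + 2 = 16 have persistent or longstanding persistent AF, and 105 − 36 = 69 have no AF history, so sparse heart-disease categories may have to be combined if the AF groups stay small. Table 1 does not list rhythm on arrival, so the rhythm of each recording must be available from the mapping data.
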